Previous research investigating the impact of early mobilization has examined patient outcomes in relation to age, stroke severity, and specific rehabilitation parameters, including intensity, duration, frequency, and timing of interventions [16,17,18]. It has also been suggested that optimal rehabilitation parameters should be tailored to the individual’s disease status and clinical characteristics [19]. Furthermore, considering both intensity and duration as components of physical activity may enable a more precise quantification of rehabilitation interventions, potentially leading to optimized clinical outcomes [13]. The acute phase of stroke is characterized by hemodynamic instability, rapid neurological deterioration, and accelerated skeletal muscle wasting, which can begin within hours of onset and progress by approximately 2% per day in severely ill patients [7]. During this period, patients are also at high risk for complications such as pneumonia, deep vein thrombosis, and pressure ulcers, all of which are exacerbated by immobility [9]. Therefore, timely initiation of rehabilitation is considered crucial not only to prevent secondary complications and muscle atrophy but also to maximize the potential for neurological recovery. This critical window highlights the need to carefully evaluate the appropriate dose and timing of early mobilization interventions. However, there is currently no consensus on the ideal dose, intensity, or timing of early mobilization for stroke patients in the acute phase. Each healthcare facility is thus exploring these parameters independently in pursuit of best practices [11]. Notably, there have been no large-scale studies in Japan evaluating the optimal daily dose of rehabilitation for stroke patients, nor have there been investigations focusing on the dosage of early-stage rehabilitation interventions.

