### 2.8. Baseline Characteristics and Treatment

The baseline characteristics of enrolled patients will be prospectively collected, including baseline factors such as age, height, weight, handedness, employment status, existing comorbidities, pre-admission mRS, and frailty; disease factors such as culprit vessel, lesion, and national institutes of health stroke scale [31]; biochemical data such as C-reactive protein, lymphocyte count, and serum albumin; and nutrition factors such as the Malnutrition Universal Screening Tool [32] at admission. The National Institutes of Health Stroke Scale will be recorded at admission, day 7, and at discharge. Details of treatments that may affect outcomes, such as surgery, use of Tissue Plasminogen Activator, noninvasive ventilation, mechanical ventilation, and tracheostomy, will also be prospectively collected.

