### 2.13. Rehabilitation Dose

Rehabilitation dose is defined using the MQS over days 1–7 post-admission. MQS combines mobilization level (assessed using the ICU mobility scale [33]) and duration (measured with a stopwatch). Only active mobilization time is included; preparation or rest is excluded. The MQS is averaged across the first 7 days to reflect the daily rehabilitation dose (Japanese version MQS [21]. It should be noted that rehabilitation itself continues beyond the first 7 days until hospital discharge, according to each institution’s standard practice. After discharge, patients typically continue rehabilitation in post-acute care facilities or outpatient/community settings, depending on their medical condition and regional healthcare resources. Functional outcomes at 90 days will therefore reflect the combined effect of early inpatient rehabilitation and subsequent standard care.

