### 2.14. Statistical Methods

There is no maximum sample size for this study; however, the outcome may be subject to targets or maximum sample sizes, which will be specified in the relevant sub-protocol. The expected sample size is ≥200 patients (minimum 10 patients/facilities, ≥20 facilities) to provide a sufficient number of different rehabilitation doses to predict functional outcomes and build robust models for protocol use. To avoid over-representation of some centers, data collection is limited to 50 patients per facility. Patient enrollment will therefore not be strictly equal across hospitals; each facility is expected to enroll at least 10 patients, with a maximum of 50 patients, depending on their clinical volume. This strategy ensures diversity in practice patterns while preventing over-representation of any single center. The number of enrolled patients and facilities is a sufficient sample size to capture the various variations in practice and treatment. It is considered feasible to collect a sample of this calculated size because each participating facility should be able to enroll at least one patient per month based on the number of stroke patients hospitalized at each facility in the past.

Baseline characteristics and outcomes will be summarized using descriptive statistics. Continuous variables will be presented as means with standard deviations (SDs) or medians with interquartile ranges (IQRs), while categorical variables will be presented as frequencies and percentages (*n*, %).

The primary analysis will examine the association between the mean rehabilitation dose (MQS score) during the first 7 days of hospitalization and the primary outcome of a favorable functional outcome (mRS ≤ 2) at 90 days. This association will be evaluated using a multivariable logistic regression model. The model will be adjusted for a pre-specified set of covariates selected for their established prognostic significance, including age, sex, pre-admission mRS, baseline National Institutes of Health Stroke Scale (NIHSS) score, stroke subtype (ischemic or hemorrhagic), and participating facility (as a random effect).

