For secondary outcomes, multivariable linear regression models will be used for continuous variables, such as the Barthel Index. A pre-specified subgroup analysis will be conducted to explore whether the effect of rehabilitation dose is modified by initial stroke severity. An interaction term between the MQS score and the severity category (defined by baseline NIHSS) will be introduced into the primary model.

Time-to-event outcomes will be analyzed using Kaplan–Meier curves and Cox proportional hazards regression models, adjusted for baseline characteristics. For survival analysis, patients will be stratified into groups based on quartiles of rehabilitation volume and pre-defined stroke severity categories. Missing data for covariates will be handled using multiple imputation under the missing-at-random assumption. The primary analysis will be based on the pooled results from the imputed datasets, with a complete-case analysis performed as a sensitivity analysis.

All statistical analyses will be performed using JMP (version 13.0; SAS Institute, Cary, NC, USA) and IBM SPSS software (version 23.0; IBM, Armonk, NY, USA). A two-sided *p*-value of <0.05 will be considered statistically significant.

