By quantifying early rehabilitation dose with MQS over days 1–7 and linking it to 90-day outcomes, this protocol is designed to yield directly actionable outputs for practice. First, clinicians can translate MQS into severity-specific dose targets during daily rounds, facilitating individualized prescriptions rather than one-size-fits-all approaches. Second, routine rectus femoris ultrasound enables early detection of muscle atrophy and dose adjustment when deterioration is observed. Third, aggregating MQS and outcomes at the facility level provides benchmarking metrics that support quality-improvement cycles and alignment across centers. Finally, these data can inform guideline refinement and the design of future randomized trials by identifying dose bands and patient subgroups most likely to benefit.

Nevertheless, some limitations must be acknowledged. First, as an observational study, causal relationships cannot be definitively established. Second, rehabilitation practices are not standardized across facilities, which may introduce variability. However, this also enhances external validity by reflecting real-world conditions. Finally, the use of telephone interviews for follow-up assessments may be susceptible to recall bias, although structured questionnaires and clear documentation (e.g., who assisted in responses) aim to minimize this limitation [37].

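### Neurological change between admission and first mobilization is neither measured nor adjusted for, so it can bias the MQS odds ratio upward overall and within severity strata

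*Protocol article*

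**What the plan says.** Section 2.14 of the protocol article fits a logistic model for mRS ≤ 2 at 90 days on mean MQS, with covariates "including age, sex, pre-admission mRS, baseline National Institutes of Health Stroke Scale (NIHSS) score, stroke subtype (ischemic or hemorrhagic), and participating facility". The severity analysis extends this model: "An interaction term between the MQS score and the severity category (defined by baseline NIHSS) will be introduced into the primary model". Its stated purpose is "to explore whether the effect of rehabilitation dose is modified by initial stroke severity".

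The timing comes from three other sections:
- **Severity (section 2.8).** "The National Institutes of Health Stroke Scale will be recorded at admission, day 7, and at discharge".
- **Dose (section 2.13).** "Rehabilitation dose is defined using the MQS over days 1–7 post-admission", averaged to a daily value. Section 2.5 requires rehabilitation to begin by day 2.
- **Acute treatment (section 2.8).** The data collection covers "Details of treatments that may affect outcomes, such as surgery, use of Tissue Plasminogen Activator" and ventilatory support. None of these is a named covariate in section 2.14. The Discussion's wider list of controlled factors (comorbidities, nutrition, rehabilitation policy, staffing) does not include them either.

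The Introduction describes the period in question: "The acute phase of stroke is characterized by hemodynamic instability, rapid neurological deterioration". The Discussion states the intended use of the result: "clinicians can translate MQS into severity-specific dose targets during daily rounds".

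**The concern.** Two patients with the same admission NIHSS can differ considerably by the first session. One improves after thrombolysis or surgery, is mobilized more and does well. The other deteriorates, is mobilized less and does badly. Given the admission score, higher MQS then goes with better outcome even if dose does nothing. Admission NIHSS cannot remove this, because the change happens after it is recorded. The day-7 score comes when the exposure window closes and may itself reflect dose.

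The bias reaches the primary odds ratio as well as the stratum-specific ones. In each stratum it points toward more being better. The Introduction expects patients with severe stroke to do better with moderate doses, so in that stratum a spurious benefit would run against the study's own hypothesis and into the dose targets promised in the Discussion. An analysis plan can add covariates that were collected, but it cannot recover a score that was never taken.

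**Working it through.** The plan gives no figure on this point to reproduce. Its only design figure, at least 200 patients (10 per facility × 20 facilities = 200), bears on precision and not on bias.

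**Model under a true null.** Let A be admission NIHSS, U the change from admission to first mobilization, and S the severity stratum.
- Dose: D = −g(A + U) + e, with e ~ N(0, 1), standardized before fitting.
- Outcome: logit P(mRS ≤ 2) = 2.0 − 0.25(A + U), with no dose term.
- Fitted: logistic regression on D, S, D×S and A. Age, sex, pre-admission mRS, stroke subtype and facility were not simulated.

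**Inputs, all assumed and none from the documents.** 40% severe; A about 15 (SD 4) in severe and 5 (SD 2.5) in mild; SD of U from 0 to 5 points; g = 0.1 or 0.2; 400,000 simulated patients.

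**Hand check, SD of U = 3 in both strata.** Given A, the approximate dose coefficient is 0.25·g·σ²/(1 + g²σ²) per unit of D.
- The variance of A + U is 24 (between strata: 0.4 × 0.6 × 10²) + 10.15 (within: 0.4 × 16 + 0.6 × 6.25) + 9 = 43.15.
- g = 0.1: 0.225/1.09 = 0.206. SD of D = √(1 + 0.01 × 43.15) = 1.196. OR per SD ≈ exp(0.247) = 1.28.
- g = 0.2: 0.45/1.36 = 0.331. SD of D = √(1 + 0.04 × 43.15) = 1.651. OR per SD ≈ exp(0.546) = 1.73.

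The simulated values (1.24–1.26 and 1.67–1.70) are close and slightly smaller.

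**Simulated OR per SD of dose (truth 1.00; range over the two values of g)**

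| Early change U | Mild | Severe | Severe/mild ratio |
|---|---|---|---|
| None | 1.00 | 1.00 | 1.00 |
| Severe only, SD 4 | 1.03–1.09 | 1.39–1.89 | 1.35–1.73 |
| Mild only, mean +1, SD 2 | 1.11–1.25 | 1.01–1.04 | 0.83–0.91 |
| Both, SD 3 | 1.24–1.67 | 1.26–1.70 | 1.01–1.02 |
| Severe SD 5, mild SD 2 | 1.14–1.41 | 1.60–2.37 | 1.40–1.68 |
| Mild SD 4, severe SD 2 | 1.41–2.03 | 1.15–1.45 | 0.71–0.81 |

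The odds ratios are pushed upward wherever early change occurs. The interaction ratio can fall above 1, below 1 or close to 1.

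**What removes the bias.** Assume g = 0.15 and a 5-point treatment response, with 40% of severe and 10% of mild patients treated.

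| Adjustment | No other early change (mild / severe) | Other early change, SD 3 (mild / severe) |
|---|---|---|
| As planned | 1.10 / 1.26 | 1.50 / 1.68 |
| Plus acute treatment | 1.01 / 1.00 | 1.43 / 1.43 |
| Plus change before mobilization | 1.00 / 1.00 | 1.00 / 1.02 |

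Adjusting for treatment is enough only when treatment response is the sole source of change. With other change present it removes the false interaction but leaves the inflated odds ratios.

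**Excluding treated patients.** A second model assumed 20–30% of patients with admission NIHSS of 5 or more treated, half of them losing 60% of their score, 10% of the rest worsening by 5 points, and MQS noise SD 5. As planned, the odds ratios were 1.11–1.13 (mild-moderate) and 1.65–1.80 (severe). Without treated patients they were 1.06 and 1.05–1.07.

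**The case against.** The strongest reply is that admission NIHSS is the correct modifier. The subgroup question concerns initial severity, and the admission score measures that before exposure accrues. A patient who arrives with a high score and recovers quickly was initially severe and is not misclassified. This stands: replacing the modifier would change the question. The fault lies in confounding of dose, not in the choice of modifier.

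A reader might also infer that rapid responders to thrombolysis or surgery necessarily create a false benefit concentrated in severe stroke. The documents do not support that:
- They do not state whether the admission NIHSS precedes thrombolysis or surgery. Section 2.3 says only that data collection begins after consent is sought within 24 hours.
- They give no rates of treatment, response or deterioration. A severe-stratum excess appears if responders are assumed to lose a fixed proportion of their score, which is largest in severe patients by construction. With deterioration alone, the second model gave 1.08 (mild) and 1.06 (severe), so no false interaction. The first table shows a reversal when mild patients change more.
- The size depends on the assumed MQS noise. With SD from 2 to 8 in the second model, the severe-stratum OR ran from 3.33 down to 1.38.

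A further reply is that the interaction test at about 200 patients would hardly notice. Under the second model there would be about 37 severe patients with about 4 favorable outcomes, and in 1,000 simulated trials the false interaction reached p < 0.05 in 5.4% and 5.0% (noise SD 4 and 6), which is the nominal rate. That stands for the test. It does not clear the primary or stratum odds ratios, whose bias does not shrink with sample size.

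Finally, rehabilitation may start on day 1, close to the admission score. The section 2.14 covariate list opens with a word that allows additions, the analysis is exploratory, and the Discussion concedes non-causality. These points lower the severity. None of them supplies a score between admission and day 7.

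**Conclusion.** The concern holds as unmeasured confounding of dose by neurological change between admission and first mobilization. Under a true null it can bias the dose odds ratio upward overall and within strata. In the scenarios of the first table with early change, stratum odds ratios ran from 1.01 to 2.37. They returned to 1.00–1.02 when the change before mobilization was added to the model.

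The direction rests on one assumption: that better neurological status at the first session leads to both more mobilization and better 90-day mRS. The size rests on assumed amounts of change, dose slopes and noise. Whether a false MQS-by-severity interaction also arises, and in which direction, cannot be determined from the article. It does not show that admission NIHSS is the wrong modifier, or that the bias falls mainly on severe stroke.

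This should be changed before enrolment starts in June 2026.

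**What to change.** 1. Keep admission NIHSS as the pre-specified modifier of initial severity.
2. Record one NIHSS after acute treatment and before the first mobilization session. Add it as a covariate in the primary and interaction models, and use it as the modifier in a sensitivity analysis.
3. Do not use day-7 NIHSS in its place, since dose may have affected it.
4. With no new data, add tPA and surgery as covariates and repeat the interaction without patients who received either before the first session. This is weaker than step 2, because it leaves other early change unadjusted.
5. Make no severity-specific dose claim unless these analyses agree with the main one.

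The cost is a few minutes of bedside scoring per patient on a scale sites already use three times, one line in Table 1 and a sentence or two in section 2.14. The no-new-data analyses cost some precision. A score before mobilization does not deal with neurological change after the first session, so that should be stated as a remaining limitation.

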### 2.11. Rehabilitation Protocol

Participants in the BRIDGE cohort will receive their usual rehabilitation at their respective institutions. We aim to exercise all participants equally every day, based on a five-stage protocol (Level 1: passive range of motion and respiratory physiotherapy, Level 2: active range of motion, Level 3: sitting exercise, Level 4: standing exercise, Level 5: walking exercise) tailored to each participating hospital. In addition, adverse events during implementation will also be indicated with appropriate values in the categories of medical, cardiovascular, respiratory, and neurological problems. In case of deviation from these values, the patient will be immediately placed on bed rest, and the event will be considered an adverse event. After level 5 is achieved, a physiotherapist or occupational therapist will provide each patient with rehabilitation, including muscle strengthening, balance, walking, and stair climbing, for at least 20 min on weekdays, according to the rehabilitation policy of each hospital.

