**ENROLMENT**				
Eligibility screen	×			
Informed consent	×			
Cohort enrollment (index date)	×			

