**ASSESSMENTS:**				
Baseline variables	×			
Muscle cross-sectional area muscle thickness	×	×		
Physical functions (Clinical Frail Scale)	×	×	×	×
Physical functions (Functional status score-ICU, Barthel index)		×	×	
Muscle strength (Medical Research Council, Handgrip)		×	×	
mRS	×	×	×	×
Exposure ascertainment (MQS; mean of Days 1–7)		×	×	

Abbreviations: ICU; intensive care unit, mRS; modified Rankin Scale, MQS; Mobilization Quantification Score.

**Table 2 jcm-14-06786-t002:** Details of outcome measures at follow-up.

Variable	Description
Survival	If a patient dies during follow-up, date of death is recorded
Employment status	Whether the patient/family has a job at follow-up (full-time or part-time) and whether the job is the same as before hospital admission
General information	Readmission to hospital during follow-up
National Institutes of Health Stroke Scale	The National Institutes of Health Stroke Scale is a 15-item impairment scale, intended to evaluate neurologic outcome and degree of recovery for patients with stroke. The scale assesses level of consciousness, extraocular movements, visual fields, facial muscle function, extremity strength, sensory function, coordination, language, speech, and hemi-inattention.
Physical function/activities of daily living	
mRS	The mRS ranges from 0 (no symptoms) to 6 (death) and is the most widely used functional outcome measure in stroke trials. An mRS ≤ 2 at 90 days is defined as a favorable outcome.
Clinical Frail Scale	The Clinical Frailty Scale is a judgment-based frailty tool that evaluates specific domains, including comorbidity, function, and cognition, to generate a frailty score ranging from 1 (very fit) to 9 (terminally ill).
FSS-ICU	The FSS-ICU is a performance-based measure that assesses physical function in critically ill patients. It evaluates five tasks: (1) rolling, (2) supine to sit transfer, (3) sitting at the edge of the bed, (4) sit to stand transfer, and (5) walking. Each task is scored from 0 (unable to perform) to 7 (complete independence), for a total score ranging from 0 to 35. Higher scores indicate better physical function.

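### Survival groups are formed from a dose that accrues after the index date, so week-1 deaths tend into the lowest quartile and tilt the comparison towards a protective dose effect

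*Protocol article*

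**What the plan says.** All references are to the Protocol article.

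- **Method (2.14):** "Time-to-event outcomes will be analyzed using Kaplan–Meier curves and Cox proportional hazards regression models, adjusted for baseline characteristics".
- **Grouping (2.14):** "For survival analysis, patients will be stratified into groups based on quartiles of rehabilitation volume and pre-defined stroke severity categories". Rehabilitation volume is not defined there, and neither the event nor the time origin is named.
- **Dose (2.13):** "Rehabilitation dose is defined using the MQS over days 1–7 post-admission", and "The MQS is averaged across the first 7 days to reflect the daily rehabilitation dose". No rule covers patients who die or leave before day 7.
- **Timing (Table 1):** the row "Cohort enrollment (index date" is marked only in the hospital admission column (T0). The row "Exposure ascertainment (MQS; mean of Days 1–7" is marked at day 7 (T1) and at discharge (T2).
- **Mortality data (Table 2):** "If a patient dies during follow-up, date of death is recorded".
- **Safety deviations (2.11):** "In case of deviation from these values, the patient will be immediately placed on bed rest".

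**The concern.** A patient's quartile is known only once week 1 is over, but on the natural reading of Table 1 the patient is already at risk of death from admission. Accruing a full week of dose requires surviving the week. Someone who dies on day 3 has at most three days of dose, so early deaths are drawn towards the low-dose group by construction. This is immortal-time bias. Baseline adjustment does not remove it, because it arises from exposure time after baseline.

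The error favours more rehabilitation. The Introduction cites a study in which very early mobilization went with poorer outcomes and more adverse events, and the Discussion foresees severity-specific dose targets and input to guidelines. The limitations paragraph says that causality cannot be established in an observational study, but does not mention this artefact.

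**Working it through.** **1. The plan's own figure.** Section 2.14 expects at least 200 patients: 10 per facility × 20 facilities = 200, which reproduces. No event count, hazard ratio or power is given for the survival analysis. The checks use N = 200, plus N = 600, the cap for the twelve hospitals of sections 2.1 and 2.3 (12 × 50).

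**2. Does eligibility protect week 1?** Not fully (2.5). An expected stay of at least 7 days is a forecast. Starting rehabilitation by day 2 protects at most the first two days. Excluding terminal-care patients lowers early deaths but does not rule them out.

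**3. Why the divisor matters.** Take a death at the end of day 3.
- Constant daily dose *d*: dividing by 7 gives 3*d*/7 = 0.43*d*; dividing by days alive gives *d*, with no truncation.
- Illustrative dose rising 1, 2, …, 7: a survivor's mean is 28/7 = 4. The early death scores 6/7 = 0.86 with divisor 7, or 6/3 = 2 over days alive. Both are too low.

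**4. Simulation under a null dose.** Dose is unrelated to death, the clock starts at admission, and the test is a Cox trend test over dose quartiles at two-sided 0.05. Assumed, because the article gives none of it: week-1 mortality 1–5%, 90-day mortality 5–15%, patient dose coefficient of variation 0.6. The first results have no rise in dose over the week, at N = 200:

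| Deaths, week 1 / day 90 | Week-1 deaths in Q1 (divisor 7) | HR Q4 vs Q1 (divisor 7) | False positives, divisor 7 | Days alive | Day-7 landmark |
|---|---|---|---|---|---|
| 1% / 10% | 65% | 0.80 | 6.4% | 4.8% | 5.0% |
| 2% / 10% | 65% | 0.65 | 12.1% | 5.4% | 5.2% |
| 3% / 10% | 63% | 0.52 | 21.6% | 5.3% | 5.3% |
| 5% / 15% | 64% | 0.50 | 32.7% | 5.4% | 5.2% |

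By chance, 25% of week-1 deaths would fall in Q1. If week-1 deaths occur only on days 2–7, about 51% fall there, the hazard ratios for the same four rows are 0.88, 0.73, 0.62 and 0.59, and false positives with divisor 7 are 5.5%, 8.8%, 13.0% and 20.6%. At N = 600 with 2% / 10%, the divisor-7 rate is 24%. The excess rejections are almost all in the protective direction.

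**5. Hand check of the 3% / 10% row.** 200 × 3% = 6 week-1 deaths and 200 × 10% = 20 in all, so 14 come later. Q1 receives 0.63 × 6 = 3.8 early deaths plus about 14/4 = 3.5 later ones: 7.3 of 50, or 14.6%. Each other quartile averages (6 − 3.8)/3 + 3.5 = 4.2 of 50, or 8.5%. The ratio of about 0.58 for an inert dose agrees with the simulated 0.52 for Q4, which receives the fewest early deaths.

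**6. Dose rising over the week.** At 3% / 9%, false positives are 27% (divisor 7) and 16% (days alive); at 5% / 15%, 40% and 23%. With deaths only after day 2 at 3% / 9%, they are 20% and 10%. Across all the ramps tried, with 1–5% week-1 mortality, divisor 7 reaches about 55% and days alive about 39%. The landmark stays at about 4–6% throughout.

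**The case against.** The strongest reply is that the premises are partly inferred. Section 2.14 names no event, no time origin and no definition of volume; the index date in Table 1 is an enrollment row; and handling of deaths before day 7 could sit in an analysis plan that is not shown. That stands as a limit: the point is conditional on time running from the index date. It does not remove the point, because the article itself fixes the grouping and defines only one dose, which is complete only at day 7.

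Stronger readings that a reader might infer, and why they do not hold:

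- **That the analysis will show a survival benefit.** In the no-ramp simulations with 1–3% week-1 mortality, about 78–94% of null studies of 200 would not reject.
- **That every week-1 death lands in the lowest quartile.** With divisor 7 about 50–65% do.
- **That the divisor is irrelevant.** Dividing by days alive nearly removes the mechanical bias if daily dose is flat. The five levels in 2.11 make a rise plausible, but the article gives no daily MQS.
- **That bed rest after a safety deviation is part of the same bias.** It is confounding by deterioration. A landmark does not remove it for patients who worsen in week 1 and die later.
- **That the primary model is equally affected.** Early deaths (mRS 6) do carry truncated dose there, but the simulated spurious odds ratio is only 1.03–1.12 per SD. Restricting that model to survivors would discard the deaths in which early harm could show.
- **That cells will be too sparse, or that quartiles must go.** Section 2.14 gives no number of severity categories and does not say they are crossed with quartiles. Quartiles also suit the hypothesis of benefit from moderate doses in severe stroke.

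Survival is also not among the outcomes listed in 2.6 and 2.7, which limits the weight of the point.

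**Conclusion.** The point holds in conditional form. Followed as written, with time from the index date, the survival analysis classifies patients by later exposure and is biased towards a protective dose effect. The direction is firm; the size is not. With a null dose, N = 200 and assumed week-1 mortality of 1–5%, the false-positive rate with divisor 7 ranges from about 5% (1% mortality, deaths only on days 2–7) to about 55% (high early mortality and a rising dose). With a days-alive divisor it is near nominal unless dose rises over the week. A day-7 landmark returns it to about 5% in every scenario. Mortality, dose variability and any ramp are assumptions; the event (death) and the time origin (admission) are inferred from Tables 2 and 1. The point concerns the time-to-event analyses and does not overturn the primary analysis.

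**What to change.** In section 2.14:

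1. Name the event and the time origin. Start time-to-event analyses at day 7 in patients alive then, with follow-up to day 90, or model dose as time-varying from admission.
2. Define rehabilitation volume as the days 1–7 MQS. If it were counted to discharge, a day-7 start would not cover the accrual period.
3. State the MQS divisor, with a rule for patients who die or leave before day 7.
4. Report deaths in days 1–7 descriptively.
5. Keep the primary mRS model in all enrolled patients and add a sensitivity analysis in day-7 survivors.
6. State that confounding from deterioration within week 1 remains after the landmark.

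The cost is wording only, since enrollment is scheduled to begin in June 2026. The price of the landmark is that survival results are conditional on surviving 7 days and leave out the week-1 deaths (1–5% of patients under the assumptions used here).
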